#### Physical activity and sedentary behaviours

Children and parents measure prospectively their total physical activity using a pedometer (Yamax Digi-Walker SW-200) over a 7-day interval that overlaps with their dietary intake recording. Families receive training on proper pedometer positioning, data recording, and other physical activity monitoring details before the measurement interval starts. To ensure proper functioning, all pedometers are calibrated prior to use by way of a standardized step count test. Since pedometers do not capture information regarding physical activity intensity, children and parents complete simultaneously a 7-day physical activity record to document quality, quantity, and patterns of moderate-to-vigorous physical activity, leisure-time screen time (television, computer, video game, etc.), and sleep duration. Once records are returned, data are reviewed with families to ensure completeness and clarify durations and intensities of activities.

#### Fasting blood sample

A fasting blood sample (~3 ml) is retrieved from children to assess total cholesterol, HDL-cholesterol, LDL-cholesterol, triglyceride, insulin, and glucose levels. Using insulin and glucose values, the homeostatic model of insulin resistance (HOMA-IR) is calculated [79]. Blood collections may occur at a number of different community-based laboratories in the Edmonton-area; however, all analyses are completed centrally at the University of Alberta Hospital laboratory to ensure the same analytical procedures are used throughout the duration of this trial.

#### Blood pressure

With children in the seated position (and following a five minute rest), systolic and diastolic blood pressure (SBP and DBP, respectively) are measured oscillometrically with an appropriately-sized cuff on the right arm. SBP and DBP are measured three times with one minute intervals between each assessment. Representative values are based on the average of the three measures.

#### Questionnaires

Children complete the *Piers-Harris Children’s Self-Concept Scale (2*^*nd*^*edition) *[80] to derive an assessment of their self-concept that focuses on the self-perceptions children have of themselves and their behaviors related to others, the *Child Depression Inventory *[81] to assess depressive symptomatology, and the *Pediatric Health-Related Quality of Life (PedsQL 4.0)* to assess functioning related to physical, emotional, social and scholastic domains [82,83]. Parents complete the *Parenting Stress Index*, which assesses three subscales reflecting child and parent relationship characteristics and life stressor [84], the *Child Behaviour Checklist *[85], which probes child behavior and potential psychopathology, the *Family Adaptability and Cohesion Evaluation Scales IV,* which assesses family cohesion and flexibility dimensions, family communication and satisfaction [86], the *Lifestyle Behaviors Checklist *[87,88] to survey common parental concerns regarding children's eating behaviors, physical activity, and other weight-related behaviors, and the parent proxy report of the *PedsQL 4.0*.

#### Family enrolment, intervention dose, and attrition

The study research coordinator record several study-specific variables that will be used to populate the CONSORT diagram (Figure 1). For instance, the total number of families recruited and enrolled in the study, parent attendance at each of the PAC sessions, and time of and reason for dropping out of the study are all documented.

**Figure 1 F1:**
[figure not shown]
Participant flow diagram according to the CONSORT statement.

### Sample size

We are enrolling 90 families (n = 45 families × 2 PAC intervention arms) in this study. Based on our clinical experience, we anticipate a 33% level of attrition, which should yield post-intervention data on 60 families. With a total sample size of 60 families (n = 30 per arm), we are able to detect a minimum difference of 0.5 in BMI z-score change between the CBT and PEP intervention groups. To our knowledge, no experimental work has been done to define specific weight-related goals for pediatric obesity interventions. However, our 0.5 BMI z-score difference is based on a review by Epstein and colleagues that suggested a reduction of this magnitude is clinically meaningful [89]. Sample size calculations were completed using *PASS 2008* (http://www.ncss.com), and assumed a standard deviation (SD) of 0.83 for each group, a one-sided significance level of 0.05, and a desired power of 80%. This SD was based on preliminary findings that included pre- and post-intervention BMI z-score data [90]. Multiple linear regressions are able to detect an R^2^ value of 10% for the effect of intervention on percent change in BMI z-score at a 0.05 significance level with 80% power, assuming that the inclusion of five control variables explains 20% of the variability in change in BMI z-score.

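### With 30 families per arm the stated assumptions give about 75% power for a 0.5 BMI z-score difference, not 80%; the difference detectable at 80% power is 0.54

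*Protocol article*

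**What the plan says.** The Sample size section of the protocol article sets out the calculation in full.

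- Enrolment: "We are enrolling 90 families (n = 45 families × 2 PAC intervention arms) in this study".
- Attrition: "we anticipate a 33% level of attrition, which should yield post-intervention data on 60 families".
- Claim, resting on 30 in each arm among those completers: "we are able to detect a minimum difference of 0.5 in BMI z-score change between the CBT and PEP intervention groups".
- Assumptions: the calculation "assumed a standard deviation (SD) of 0.83 for each group, a one-sided significance level of 0.05, and a desired power of 80" per cent.

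The section takes 0.5 from a published review as a clinically meaningful reduction, so 0.5 is the target effect. The Statistical analysis section names a one-sided independent-samples t-test for the primary comparison, which agrees with the one-sided level used for the sample size.

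**The concern.** A two-group comparison of means is fixed by five quantities: difference, SD, significance level, number per arm and power. Any four determine the fifth. The section states all five, and they are not mutually consistent: the number per arm is too small for the power, or equivalently the detectable difference is larger than stated.

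The statement justifies the trial's size for its primary outcome. If the power is really 75%, a true difference of the size the trial regards as worthwhile would be missed one time in four rather than one in five. A non-significant result would also be read against a detectable difference that the design does not have.

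**Working it through.** **Inputs, from the Sample size section:** difference 0.5; SD 0.83 in each group; one-sided level 0.05; power 80%; 30 per arm after attrition, 45 per arm enrolled. The test is the one-sided two-sample t-test of the Statistical analysis section.

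**Attrition step.** 60 / (1 − 0.33) = 89.6, rounded up to 90. This reproduces, so the error is not here.

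**Power at 30 per arm.**

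- Standard error of the difference: 0.83 × √(2/30) = 0.2143.
- Noncentrality: 0.5 / 0.2143 = 2.333.
- Normal approximation: Φ(2.333 − 1.645) = Φ(0.688) = 75.4%.
- Exact noncentral t on 58 degrees of freedom: 74.6%.

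The stated 80% is not reproduced by either method.

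**Number per arm for 80% power.**

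- Normal approximation: 2 × (0.83/0.5)² × (1.645 + 0.842)² = 34.1, rounded up to 35.
- Exact t: 34 per arm gives 79.2% and 35 per arm gives 80.2%, so 35.
- That is 70 completers against 60, or 35/30 = 1.17, 17% more. At 33% attrition, 70/0.67 = 104.5, about 105 enrolled.

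**Detectable difference at 30 per arm and 80% power.**

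- Normal approximation: 0.2143 × (1.645 + 0.842) = 0.533.
- Exact t: 0.539.

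**SD that would make the claim true.** 0.78 by the normal approximation and 0.77 by exact t, against 0.83 stated.

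**Could another reading recover 80%?** Power for a difference of 0.5, exact t:

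| Reading | Power |
|---|---|
| As stated: 30 per arm, SD 0.83, one-sided | 74.6% |
| SD 0.825 (lowest value that rounds to 0.83) | 75.0% |
| SD 0.835 (upper rounding limit) | 74.1% |
| Two-sided 0.05, 30 per arm | 63.1% |
| One-sided, all 45 enrolled per arm | 88.3% |
| Two-sided, all 45 enrolled per arm | 80.7% |

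Only the last row comes near 80%. It contradicts both the one-sided level and the 30 per arm on which the section rests its claim. It may hint at where the 90 came from, but that is conjecture, and the finding does not depend on it.

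**The case against.** The arithmetic is not in dispute. Three arguments can be made for leaving the text alone or treating the matter as minor.

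*Rounding.* The detectable difference of 0.539 prints as 0.5 to one decimal. This would be a fair defence if 0.5 were only the output of the calculation. The section instead adopts 0.5 as the clinically meaningful difference, and power at 0.5 itself is about 75%.

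*Meaning of the SD.* The section says that 0.83 came from preliminary pre- and post-intervention data and does not say outright that it is the SD of the change. If it were the SD at a single time point, the SD of change would be 0.83 × √(2(1 − r)) for a pre-post correlation r. Then r of about 0.57 would give 0.77 and recover 80%, a higher r would give more power, and r below 0.5 would give less than the 74.6% found here. But the section states 0.83 as the SD entered into the calculation and gives no correlation. On its plain reading 0.83 is the SD of the quantity compared. The point supports confirming what 0.83 is; it does not rescue the sentence.

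*Size and consequence.* The gap is about 5 points of power and 0.04 z-score units. The 33% attrition is itself a forecast: 35 completers per arm out of 45, which is 22% attrition, would reach 80%. The plan also reports 95% confidence intervals, so interpretation need not rest on the planning figure alone. Moreover, the Statistical analysis section tests percent change, whereas the 0.5 is an absolute change. All this stands and limits the harm. It does not make the stated figure correct.

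**Conclusion.** The concern holds. On the section's own inputs, 30 per arm give 74.6% power for a difference of 0.5 (75.4% by the normal approximation), about 5 points below the stated 80%. The difference detectable at 80% power is 0.54, and 80% power for 0.5 needs 35 per arm.

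This assumes that 0.83 is the SD of the compared change in each arm, that the two arms are of equal size, and that the test is the planned one-sided t-test at 0.05 without covariate adjustment or allowance for clustering. No outside figure is used. The error is definite and modest in size. It affects the power statement for the primary outcome and does not invalidate the trial.

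**What to change.** Keep 90 families and replace the claim with a sentence such as: With 30 families per arm, SD 0.83 and a one-sided 0.05 test, the trial has 75% power for a difference of 0.5 in BMI z-score change; the difference detectable with 80% power is 0.54. In the same sentence, say that 0.83 is the SD of the change, if that is confirmed.

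This costs one sentence and a slightly less favourable figure, with no added recruitment. It does mean accepting less than the 80% the trial set itself, and the text should say so. If 80% is to be kept, the alternative is 70 completers, about 105 enrolled at 33% attrition, or 15 more families.

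If the sidedness of the test, the treatment of clustering or the adjustment for baseline is changed for other reasons, recompute the figure on that basis.

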### Recruitment

Families are eligible for this study if (*i*) children are between 8 – 12 years old, (*ii*) children present with an age- and sex-specific BMI ≥85^th^ percentile [50], (*iii*) at least one parent agrees to attend weekly PAC sessions for 16 weeks, and (*iv*) children and parents are fluent in English (verbal and written). Recruitment is conducted primarily through the PCWH, although we also attempt to recruit families from the greater Edmonton area through advertisements (e.g., posters on local health, community, and recreation centers, mail outs to local family and pediatric medical clinics).

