### Strengths and limitations

The current study has a number of noteworthy strengths. First, we took a rigorous and systematic approach to the design of this RCT as well as the development and refinement our intervention materials for parents and group leaders. The manualized intervention materials for group leaders, external expert review of intervention materials, and plan to evaluate intervention fidelity enhance methodological rigour and provide confidence that the interventions are distinct from one another, which is needed to evaluate their differential effects. Second, if the CBT and/or PEP versions of the PAC intervention help parents to make positive changes, the manualization of intervention materials enables the dissemination and evaluation of PAC in other settings (i.e., primary care, public health). Existing partnerships between our team members and health services (e.g., Alberta Health Services; http://www.albertahealthservices.ca) and non-governmental (e.g., Canadian Obesity Network; http://www.obesitynetwork.ca) organizations should facilitate the dissemination and future delivery of the PAC intervention within the province of Alberta and across Canada. Third, because most of the boys and girls enrolled in this study are recruited from the PCWH, they are almost exclusively described as *severely obese* (BMI ≥99^th^ percentile or BMI ≥40 kg/m^2^) [93]. Since much of the evidence in managing pediatric obesity includes less overweight and obese participants [89], the present RCT contributes important information regarding the impact of parent-based approaches for managing severe obesity in children. Finally, offering pediatric weight management interventions for parents exclusively represents an efficient model of care. Common sense dictates that the PAC interventions can be delivered using fewer resources (physical, human, financial) than interventions that include both parents and children. Since many pediatric weight management centers in Canada struggle to deliver health services with limited resources and infrastructure [14], interventions that are both efficient and effective are most desirable.

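### The sample size rests on an SD of 0.83 that is not shown to be the SD of BMI z-score change and is implausibly large for it here, so 0.5 should not be presented as the trial's detection limit

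*Protocol article*

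**What the plan says.** The Sample size section of the protocol article plans for 60 analysed families, 30 per arm, out of 90 enrolled, and says "we are able to detect a minimum difference of 0.5 in BMI z-score change between the CBT and PEP intervention groups". The inputs are "a one-sided significance level of 0.05, and a desired power of 80"%, and it "assumed a standard deviation (SD) of 0.83 for each group". On where the SD comes from, it says only: "This SD was based on preliminary findings that included pre- and post-intervention BMI z-score data". The 0.5 itself is taken from a cited review that regarded a reduction of that size as clinically meaningful.

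Two other places describe the children. Under Recruitment, families are eligible if "children present with an age- and sex-specific BMI" at or above the 85th percentile. Under Strengths and limitations, most children are said to come from the weight management clinic, and of these the article says "they are almost exclusively described as" severely obese, defined there as a BMI at or above the 99th percentile or of at least 40 kg/m².

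**The concern.** A calculation for a difference in change needs the SD of individual change. The article says that the preliminary data contained pre- and post-intervention scores, but not which SD was taken from them or in which children. The value 0.83 is large for the within-child change of a selected, high-BMI group over one programme, and is closer to what one might see for scores at a single visit.

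What is at stake is how the result is read. The article uses 0.5 both as the clinically meaningful amount and as the least the trial can detect. If the change SD is much smaller than 0.83, the trial can detect differences well below its own benchmark, and a significant result need not be a clinically meaningful one. The two arms share content, contact schedule and goals, so a difference below 0.5 is a realistic outcome.

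**Working it through.** **1. The plan's own figure.** Inputs from the Sample size section: SD 0.83, 30 per arm, one-sided 0.05, 80% power.

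- Normal approximation: (1.645 + 0.842) × 0.83 × √(2/30) = 0.533. The noncentral t gives 0.539.
- Power for a difference of 0.5 is 75.4% (normal) or 74.6% (t).
- For 80% power at 0.5, 35 per arm would be needed.
- The SD that gives exactly 0.5 at 30 per arm is 0.78 (normal) or 0.77 (t).

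The stated 0.5 is therefore not reproduced exactly, although 0.53 to 0.54 rounds to it.

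**2. What 0.83 implies as a change SD.** With the same SD s at both visits and pre-post correlation r, the SD of change is s√(2(1 − r)). Setting this to 0.83 gives s = 0.83/√(2(1 − r)):

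| r | visit SD needed |
|---|---|
| 0 | 0.59 |
| 0.5 | 0.83 |
| 0.7 | 1.07 |
| 0.8 | 1.31 |
| 0.9 | 1.86 |

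**3. What visit SD the population suggests.** The article gives none. As an assumption, take a standard normal cut off below at c. With tail mean λ, the variance is 1 + cλ − λ².

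- 85th percentile: c = 1.036, λ = 1.554, SD = 0.44.
- 99th percentile: c = 2.326, λ = 2.665, SD = 0.31.

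Even at r = 0, these give change SDs of only 0.44 × √2 = 0.62 and 0.31 × √2 = 0.44. At r = 0.8 they give 0.28 and 0.20.

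**4. Detectable difference for other change SDs.** The setting is 30 per arm, one-sided 0.05, 80% power, noncentral t. The SDs below 0.83 are assumed, because the article supplies none.

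| SD of change | detectable difference | power for 0.5 |
|---|---|---|
| 0.20 | 0.13 | >99.9% |
| 0.30 | 0.195 | >99.9% |
| 0.40 | 0.26 | 99.9% |
| 0.50 | 0.325 | 98.6% |
| 0.60 | 0.39 | 94% |
| 0.70 | 0.455 | 86% |
| 0.83 | 0.54 | 75% |

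**5. If 0.83 is a single-visit SD.** The change SD would be 0.64, 0.53 or 0.37 at r = 0.7, 0.8 or 0.9. The detectable difference would then be 0.42, 0.34 or 0.24.

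**The case against.** The strongest reply is that the source is not visible. The article attributes 0.83 to data with both pre- and post-intervention scores, which is what one would use to compute a change SD. It gives no visit SD, no correlation and no description of that sample. A reader might infer that 0.83 has been shown to be wrong, or to be a visit-level SD entered by mistake. The documents do not support either. They show a poor fit and leave the quantity undefined.

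The tail model is also only a yardstick. A referred clinic cohort need not be a truncated normal, and the BMI criterion of 40 or more can stretch its upper end. Range restriction lowers r. The measurement windows allow up to about 32 weeks between assessments (8 + 16 + 8), which could lower it further. Community recruits may enter from the 85th percentile. All of this stands, and it is why the alternative SDs are given as an assumed range. It does not remove the difficulty: at r = 0.8 the visit SD would still have to reach 1.31.

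Three further inferences should be resisted.

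- That the planned confidence intervals would be too wide. The Statistical analysis section computes them from observed data, and 0.83 does not enter.
- That a smaller SD leaves the trial underpowered. It does the opposite: any such error is conservative for enrolment.
- That significance below 0.5 is itself a defect. Any trial can reach significance below its 80%-power difference. With SD 0.83 the threshold is already about 1.67 × 0.83 × √(2/30) = 0.36.

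Finally, 0.53 to 0.54 rounds to 0.5. The rounded difference can be defended, but 80% power for 0.5 cannot.

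**Conclusion.** The concern holds in a limited form. The article does not establish that 0.83 is the SD of individual change. For the children it describes, that reading is implausible at any ordinary positive pre-post correlation, judged against an assumed normal tail.

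The stated 0.5 is not the exact 80%-power limit if 0.83 is correct (0.54), nor if the change SD lies in the assumed range of 0.2 to 0.6 (0.13 to 0.39). It would be exact only at an SD of about 0.77 to 0.78, which the article does not state. The direction depends on what 0.83 is: taken at face value the trial falls slightly short of 80% power for 0.5, and with a smaller SD it exceeds it. The fault is in how the trial's sensitivity is described and in using one number as both clinical benchmark and detection limit. It gives no reason to change enrolment.

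**What to change.** - State whether 0.83 is the SD of individual change or of a single-visit score, and in which children it was observed.
- Compute the SD of individual pre-to-post change from the team's preliminary data, for children who meet this trial's eligibility criteria and match its expected case mix. Restricting this to the 99th percentile and above would not match entry from the 85th.
- Restate the detectable difference, or the power for 0.5, at 30 per arm. Do so on the scale of the primary test: the Statistical analysis section tests percent change, whereas 0.5 and 0.83 are in z-score units. The conversion needs baseline values that the article does not give.
- Check the assumed value against the blinded pooled SD of change as data accrue.
- Describe 0.5 as the clinical benchmark against which the confidence interval is read, not as the least the trial can detect.

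The cost is one recalculation from data the team should already hold, a blinded check and a rewritten sentence or two. Enrolment stays at 90.

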### Statistical analysis

Data cleaning, analyses, figures, tables, and statistical sections for dissemination are conducted by a blinded biostatistician with the Biostatistics Consulting Group within the Women and Children’s Health Research Institute (http://www.wchri.org) at the University of Alberta. Spotfire S + 8.2 (TIBCO Software Inc, 2010) and SAS 9.3 (SAS Institute Inc, 2010) will be used for analyses. Analyses are conducted both with PAC intervention completers only and with all participants (to evaluate effectiveness). Continuous variables are described by summaries (e.g., means, medians, ranges and SDs) and frequency distributions are determined for categorical variables. For the primary and secondary outcome variables, the percent change from pre- to post-intervention (as well as 6- and 12-months follow-up) for both groups is determined and summarized along with the 95% confidence intervals (CIs) for mean percent change. Boxplots and histograms are used to display the percent change for these variables; bar charts are used for categorical variables. Our analyses are conducted separately for each mean percent change at each observation time (i.e., pre-intervention to post-intervention, pre-intervention to 6-month follow-up, and pre-intervention to 12-month follow-up). Statistical tests are set at conventional levels (p < 0.05) and all analyses are intention-to-treat. Multiple imputation methods may be used in the event of missing data. To minimize the risk of bias, a research team member with no direct contact with enrolled families is leading the data analyses.

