To compare interventions, one-sided independent samples Student’s t-test assesses percent changes in BMI z-score (primary objective); if required, data transformations are used to ensure data normality. A similar process is used to determine intervention-mediated changes in other physiological, behavioural, and psychosocial outcomes (secondary objectives). In addition, the percentage of families with improved categorical outcomes (i.e., those who do/do not meet recommendations from *Eating Healthy with Canada’s Food Guide*) is compared across interventions using a one-sided independent samples proportion tests. A multivariable linear regression model is developed for the primary outcome (percent change in BMI z-score) to determine the intervention group effect while controlling for potential confounders (i.e., cohort, percent attendance, household income). If any of the intervention groups include siblings, CIs are adjusted using variance inflation factors, and univariable or multivariable random intercept mixed effects models are used in lieu of Student’s t-tests and multivariable linear regression, respectively. Analogous calculations are made to compare the percent change from pre-intervention to 12-month follow-up, although intervention attrition may reduce our power to detect a significant difference. Mixed effect models are developed to examine the effects of the interventions on primary and secondary outcomes over time. This approach allows all pre-intervention, post-intervention, and follow-up data to be included in our modeling. For all models, residual diagnostics are used to assess model assumptions and appropriate transformations and/or non-linear terms are included as necessary. Our reporting of study results is in accordance with the CONSORT statement [91].

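### The t-tests and proportion tests between the arms are one-sided at 0.05, called conventional and left unexplained, so the CBT false-positive rate is 5% and these tests cannot declare PEP better

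*Protocol article*

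**What the plan says.** Four statements in the protocol article bear on this.

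- **Sample size.** The calculation uses "a one-sided significance level of 0.05, and a desired power of 80" per cent. It "assumed a standard deviation (SD) of 0.83 for each group" and concludes that "we are able to detect a minimum difference of 0.5 in BMI z-score change between the CBT and PEP intervention groups".
- **Statistical analysis, second paragraph.** The primary comparison opens "To compare interventions, one-sided independent samples" and goes on to name Student's t-test on percent change in BMI z-score. The other physiological, behavioural and psychosocial outcomes are handled by a similar process. Categorical outcomes get one-sided proportion tests.
- **Statistical analysis, first paragraph.** "Statistical tests are set at conventional levels (p < 0.05"). The change in each arm is "summarized along with the 95% confidence intervals (CIs) for mean percent change". No interval for the between-arm difference is described.
- **Methods/Design, opening paragraph.** The primary objective is to compare how the two programmes differ in their effect on BMI z-score, with no direction given. The same paragraph labels the trial a superiority trial, and the Background states a hypothesis that CBT will do better.

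No section gives a reason for one-sided testing. The multivariable regression and the mixed models are described without stating whether their tests are one- or two-sided.

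**The concern.** A one-sided test at 0.05 puts the whole error allowance on one side. If the arms do not truly differ, the chance of a significant result for CBT is twice what most readers expect when a plan describes its level as conventional.

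The comparator makes this matter. The protocol says that PEP is not a true control and that its content and delivery match what many clinicians provide. It also presents the trial as a comparison of two evidence-informed approaches. A finding that the existing style of programme did better than CBT would be a real result. The tests named for the primary and secondary outcomes have no rejection region on that side, so such a finding could be described but not declared by them. This applies to every outcome tested this way, at each observation time.

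The adjusted analysis of the primary outcome could also run at a different error rate from the unadjusted t-test, because its sidedness is open.

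**Working it through.** **Inputs**, all from the Sample size section: difference 0.5 in BMI z-score change; SD 0.83 in each arm; 30 evaluable per arm; one-sided 0.05; target power 80%; 90 enrolled; 33% attrition. The calculation is on absolute z-score change, whereas the planned t-test is on percent change, so the powers below hold for the planning scale only.

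**1. The plan's own figure**

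- Attrition: 90 × (1 − 0.33) = 60.3, so 60 evaluable families. This reproduces.
- Standard error of the difference: 0.83 × √(2/30) = 0.214.
- Standardised difference: 0.5 / 0.214 = 2.333.
- One-sided 0.05, normal approximation: Φ(2.333 − 1.645) = Φ(0.688) = 75.4%. The exact noncentral t (58 df) gives 74.6%.
- n per arm for 80%: 2 × (0.83/0.5)² × (1.645 + 0.842)² = 34.1, so 35 per arm. The noncentral t also gives 35. That is 70 evaluable, or 70/0.67 ≈ 105 enrolled.
- Difference detectable with 80% power at 30 per arm: 0.54. This matches 0.5 only by rounding.

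The stated 80% therefore does not reproduce at 30 per arm, even one-sided.

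**2. The same design at two-sided 0.05**

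- Normal approximation: Φ(2.333 − 1.960) = Φ(0.373) = 64.5%. Noncentral t: 63.1%.
- Detectable difference at 80% power and 30 per arm: 0.61.
- n per arm for 80%: 44 (normal) or 45 (noncentral t). With 45 that is 90 evaluable, or 90/0.67 ≈ 135 enrolled.

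**3. What one-sidedness changes**

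| | One-sided 0.05 | Two-sided 0.05 |
|---|---|---|
| False-positive rate in favour of CBT | 5% | 2.5% |
| Critical t, 58 df | 1.672 | 2.002 |
| Observed difference needed (critical t × 0.214) | 0.36 | 0.43 |
| Power for 0.5 at 30 per arm (noncentral t) | 74.6% | 63.1% |

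An observed advantage for CBT between 0.36 and 0.43 would be significant under the plan but not under a two-sided 5% test. If PEP were truly better by 0.5, the one-sided test would reject with probability of about 0.00004, and then in favour of CBT.

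**4. The regression statement**

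The Sample size section gives R² of 10% for the intervention, five control variables explaining 20%, level 0.05 and power 80%, with no sidedness and no separate N. Taking N = 60: f² = 0.10 / (1 − 0.30) = 0.143, noncentrality = 60 × 0.143 = 8.57, with 1 and 53 df.

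- Ordinary F-test at 0.05 (two-directional for one coefficient): power 82.0%; 80% is reached at N = 58.
- One-sided 0.05 equivalent (F at 0.10): power 89.3%.

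The stated 80% lies closer to the two-directional test. This is an inference from an assumed N, not something the article states.

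**The case against.** The best defence is that the choice is open and consistent. The trial is labelled a superiority trial, the hypothesis that CBT is better is stated in the Abstract, Background and Discussion, and the sample size and the tests use the same one-sided level. That stands: this is a disclosed design choice, not a hidden error. A directional hypothesis does not by itself justify allowing 5% in that direction, though, and no other reason is offered.

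It can also be said that the conventional label refers only to the number 0.05. That is a possible reading, but the description misleads when the tests are one-sided.

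Several stronger readings are tempting, and the article does not support them.

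- A reader might infer that the 95% intervals contradict the one-sided test. The intervals described are for the mean change in each arm, so they do not conflict directly with a test of the difference. A mismatch would arise only if a two-sided 95% interval for the difference were set beside the one-sided p-value.
- A reader might infer that a result favouring PEP could not be reported at all. Arm-level changes with intervals will be reported, and the regression and mixed models are not said to be one-sided. Only the named t-tests and proportion tests cannot declare it.
- A reader might take the remark that many parents prefer PEP's lower demands, or the conditional "if the CBT and/or PEP versions of the PAC intervention help parents to make positive changes" under Strengths and limitations, as a sign that PEP was expected to do better. The first concerns effort and the second concerns either programme helping. Neither says that PEP would lower BMI z-score more than CBT.
- A reader might blame sidedness for the whole fall from 80% to 63%. The stated one-sided design already gives about 75%, so sidedness accounts for about 75% to 63%. The rest is a separate shortfall in the sample-size calculation.

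**Conclusion.** The point holds in limited form. The primary t-test and the secondary t- and proportion tests are one-sided at 0.05 without justification, against an active comparator and under an objective with no direction. For the continuous secondary outcomes this rests on reading the similar process as including the one-sided test. The false-positive rate in favour of CBT is 5% instead of 2.5%, and these tests cannot declare PEP better on any outcome. The sidedness of the regression and mixed models is open, so unadjusted and adjusted analyses of the same outcome may run at different error rates.

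Power for a 0.5 difference at 30 per arm is about 75% one-sided and about 63% two-sided. These figures assume SD 0.83, equal arms, independent families and absolute z-score change. They do not carry over to percent change without an SD on that scale, which the article does not give.

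**What to change.** - Make all secondary tests two-sided at 0.05, and preferably the primary test too.
- Report the between-arm difference with an interval that matches the test: 95% if two-sided, or 90% if the one-sided primary test is kept with a stated reason.
- Do not describe one-sided 0.05 as a conventional level.
- State the sidedness of the regression and mixed models, and use the same one for unadjusted and adjusted analyses of an outcome.
- Restate power for a 0.5 difference at 30 per arm: about 75% one-sided, or about 63% two-sided with a detectable difference of about 0.61. Say that it refers to absolute z-score change.

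These changes cost only analysis wording, and the downside is a less favourable power figure. The debatable part is the primary test. Keeping 80% power two-sided would take 45 evaluable per arm, or about 135 enrolled at 33% attrition, against the 90 planned. If enrolment cannot grow, the lower power should be stated openly.
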